#### Statistical analysis

3.1.17

Data will be analyzed statistically using different tests, considering the level of significance of 5%. The data obtained will be submitted to descriptive statistical analysis to evaluate the association of categorical variables. Chi-square test and Fisher exact test will be applied, and to analyze the correlation between the continuous variables, Pearson correlation test will be applied. For the analysis of dentin density in the scanned radiographic images and the microbiological results for colony-forming units, ANOVA and Kruskal–Wallis will be applied.

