#### Specific objectives

3.1.2

To compare the use of aPDT with ART.

Hypothesis (H1): The application of Photodynamic Therapy (PDT) in permanent teeth with severe molar incisor hypomineralization, with painful sensitivity, associated with the presence of caries lesion is effective for desensitization and decontamination of the cavities.

Hypothesis (H0): The application of Photodynamic Therapy (PDT) reduces the number of viable bacteria, but is not effective in the treatment of painful sensitivity.

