#### Evaluation of dentin sensitivity—primary outcome

3.1.12

Before removal of the carious dentin, Group 1 and Group 2 volunteers will respond to the Visual Analogue Scale (VAS),^[38]^ which will obey the following protocol: gauze isolation of neighboring teeth; light air jet in the tooth with MIH for 2 seconds; sensitivity evaluation through the VAS scale. This sequence will be repeated at the end of the procedure, after insertion of the glass ionomer cement.

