#### Radiographic evaluation

3.1.14

Interproximal radiographs will be performed initially, aiming at assessing the presence of caries on the proximal surface (adjacent surfaces), radiolucency compatible with carious lesion in dentin, deep caries and to rule out the possibility of pulp involvement. Hereafter, the controls will be in 6 and 12, to analyze the optical density and visual clinical interpretation of the remaining dentin, even as the evaluation with the radiographic subtraction technique.^[40]^ All images will be made with KODAK Double Films. To better understand the application of the radiographic subtraction technique, the 4 radiographs will be compared and must be taken with the minimum geometrical distortion, which is achieved by individualizing prefabricated radiographic film positioners by means of occlusal records with self-curing acrylic resin, specific for each patient. These should be stored for subsequent radiographic shots.

The radiographic processing should be standardized, such as the time of radiographic exposure, kilovoltage and mili-amperage of the apparatus, and type of film, in order to obtain density and contrast as “identical” as possible between the images.^[40–42]^ The standardization of radiographic processing will be used and the same time of revealing, intermediate washing, fixation, and final washing, in all periods, should be the same. The chemicals used will be Kodak. The images obtained radiographically in the different intervals will be scanned for analysis of the density difference between them. To do so, the program Imagelab 2.3^[41]^ will be used. Thus, it is expected that the density of the remaining dentin will follow the variations in optical density, so they will be evaluated in the time intervals between 6 and 12 months after therapeutic application in all groups. The objective will be to quantitatively determine the gray tones of the affected dentin region just below the restoration in glass ionomer and compare the density of the remaining dentin in both groups.^[41–44]^

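### The analysis section gives the VAS primary outcome no between-arm comparison, and does not say how ANOVA and Kruskal–Wallis will handle repeated CFU and density readings on the same tooth

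*Protocol article*

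**What the plan says.** Section 3.1.12 is headed "Evaluation of dentin sensitivity—primary outcome". It has both groups rate sensitivity on the VAS, after an air jet, before carious dentin is removed. A second reading follows: "This sequence will be repeated at the end of the procedure, after insertion of the glass ionomer cement". Each tooth therefore has two VAS values.

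The comparison of interest is in section 3.1.2: "To compare the use of aPDT with ART". The hypotheses there turn on sensitivity, because the null already grants a bacterial reduction and denies only an effect on painful sensitivity.

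Section 3.1.17 then allocates methods:

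- Categorical variables: chi-square and Fisher exact tests.
- Continuous variables: "to analyze the correlation between the continuous variables, Pearson correlation test will be applied".
- Dentin density and CFU: "the microbiological results for colony-forming units, ANOVA and Kruskal–Wallis will be applied".

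VAS is not named. The Methods paragraph of the abstract gives the same list.

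CFU is sampled before and immediately after removal of carious tissue (3.1.13). Density is followed at 6 and 12 months, and section 3.1.14 states the aim to "compare the density of the remaining dentin in both groups".

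**The concern.** The outcome on which the hypotheses rest has no stated test of one arm against the other, while secondary outcomes are named and given tests. A t-test, a rank test, a change score or a within-arm before/after test could each be chosen once the data are known, and these can give different answers.

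For CFU and density the difficulty is narrower. Both are measured more than once on the same tooth. The section does not say what enters the test, and it names no baseline-adjusted or group-by-time contrast. Some uses of the named tests answer the aPDT-versus-ART question correctly, and others do not.

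**Working it through.** **Inputs.** 24 teeth per group (3.1.9) and a 5% significance level (3.1.17). The article prints no standard deviation or within-tooth correlation, so correlations ρ of 0.3, 0.5 and 0.7 are assumed throughout. It prints no figure on this point that could be reproduced.

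**1. VAS against the list of methods.** VAS is a continuous score. Chi-square and Fisher are for categories, and ANOVA and Kruskal–Wallis are assigned to density and CFU. That leaves Pearson, which gives a correlation coefficient and no difference between arms.

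**2. CFU and density: what each use of the tests would do.**

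*One value per tooth (a change or a single visit), compared between arms.* This is valid. In simulation (3,000 runs per setting, normal data, 24 teeth per arm, ρ from 0 to 0.7), Kruskal–Wallis on the before-to-after change rejected a true null in 4.8% to 5.4% of runs.

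*Several visits pooled as independent values, compared between arms.* With m visits per tooth, the true variance of the arm difference is 1 + (m − 1)ρ times the variance assumed. The actual two-sided error is 2[1 − Φ(1.96/√(1 + (m − 1)ρ))].

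| ρ | m = 2: 1.96/√(1+ρ) | Error | m = 3: 1.96/√(1+2ρ) | Error |
|---|---|---|---|---|
| 0.3 | 1.96/√1.3 = 1.72 | 8.6% | 1.96/√1.6 = 1.55 | 12.1% |
| 0.5 | 1.96/√1.5 = 1.60 | 11.0% | 1.96/√2.0 = 1.39 | 16.6% |
| 0.7 | 1.96/√1.7 = 1.50 | 13.3% | 1.96/√2.4 = 1.27 | 20.6% |

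Simulated errors for m = 3 (4,000 trials per setting) were 12.3%, 16.8% and 21.4%.

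*Four cells, arm by time, in one omnibus test.* With no arm effect and a common fall of 1 SD in both arms, Kruskal–Wallis rejected in 98% to 100% of runs. Such a rejection is correct, because time differs, but it says nothing about aPDT against ART.

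*Before against after within one arm, pairing ignored.* The error falls below nominal: 2.3%, 0.7% and 0.0% at ρ = 0.3, 0.5 and 0.7. Power suffers too: for a 0.7 SD shift at ρ = 0.5 it was 69%, against 91% for the paired Wilcoxon test.

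**3. What baseline adjustment gains.** Relative to comparing post values alone, ANCOVA multiplies the variance by 1 − ρ².

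- ρ = 0.5: 1 − 0.25 = 0.75, a 25% cut. 24 teeth per group do the work of 24/0.75 = 32.
- ρ = 0.7: 1 − 0.49 = 0.51, a 49% cut. 24 teeth do the work of 24/0.51 ≈ 47.

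Relative to a change score, with variance 2(1 − ρ), the ratio is (1 + ρ)/2. That is 0.75 at ρ = 0.5 and 0.85 at ρ = 0.7, so the gain is smaller (25% and 15%).

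**4. Whether VAS is available in both arms.** The Group 1 steps (3.1.7.1) list a VAS reading before and after treatment. The Group 2 steps (3.1.7.2) list none, although section 3.1.12 requires both readings in both groups.

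**The case against.** A reader might infer that the protocol applies one-way, independent-group ANOVA to repeated readings, and that its false-positive rate is therefore 12 to 21%. The document does not support that. Section 3.1.17 says only ANOVA, which could be a repeated-measures ANOVA, and either named test is sound between arms on changes or at one visit. No section proposes pooling visits or reading a four-cell test as an arm effect. The three-visit figures also need a usable initial density reading. Section 3.1.14 targets dentin just below the restoration, which does not exist on the initial film, so two visits may be the more realistic case. Nor can it be said that the CFU and density comparisons are necessarily untested; that depends on how the tests are applied.

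It can also be said that comparing post values alone is unbiased in a randomised trial, that naming a parametric and a rank test together is common shorthand, and that a condensed article leaves model details to fuller documents. Procedure time, too, has no named between-arm test, which suggests that the list is not exhaustive.

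All of this stands for CFU and density, and it limits that part to a risk of the wording. It does not remove the VAS point. The section does allocate methods by variable, and the only one that could cover the primary outcome cannot make the comparison in section 3.1.2.

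**Conclusion.** The concern holds in two parts of different strength.

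- **VAS: firm.** As written, the primary outcome has no between-arm comparison. This follows from setting sections 3.1.2, 3.1.12 and 3.1.17 side by side and needs no assumption.
- **CFU and density: an ambiguity with a real downside.** Kruskal–Wallis is valid between arms only on one value per tooth, and the section does not say that this is what will be analysed. If repeated raw readings were entered as independent, the error could run at about 9 to 13% (two visits) or 12 to 21% (three), or below 5% in a within-arm comparison. These figures rest on assumed correlations of 0.3 to 0.7 and normal data, and describe possible misuse.

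The case for baseline adjustment is one of precision: a variance cut of about 25% to 49% against post-only analysis, at assumed before-after correlations of 0.5 to 0.7.

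**What to change.** Amend section 3.1.17, and the matching sentences in the abstract, along these lines:

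- **Primary analysis:** ANCOVA of post-procedure VAS on group and pre-procedure VAS, reporting the adjusted mean difference with its 95% confidence interval, and a rank-based ANCOVA as sensitivity analysis.
- **CFU:** ANCOVA of post-removal log10 CFU on group and baseline log10 CFU.
- **Density:** a linear mixed model for the 6- and 12-month values with group, visit, group-by-visit and a random intercept per tooth. Initial density should enter as a covariate only if the same region can be measured on the initial film.
- **Pearson:** keep for stated exploratory correlations only.

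These replace ANOVA and Kruskal–Wallis for the repeated readings. The cost is analysis wording, with one condition. The Group 2 step list in 3.1.7.2 and the VAS requirement in 3.1.12 must be reconciled, because the primary comparison cannot be run without VAS readings in both arms.

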## Discussion

4

Often in the presence of MIH, the occurrence of dentin sensitivity is also associated with caries lesion, making it even more necessary to respect the principles of minimal intervention. According to some authors in situations of deep lesions associated with MIH (especially at risk of pulpal exposure) the selective removal of soft dentine should be applied, that is, removal of this soft tissue only from the surrounding walls, maintaining the soft dentine of the wall pulpar.^[16]^ Since contaminated tissue is kept inside the cavity in these situations, the application of decontamination methods such as PTT is necessary. Some studies suggest that the use of the PapaMblue gel in aPDT is effective, in addition to producing more toxic oxygen species than the free methylene blue.^[36]^
